**Methods:**

Randomized controlled trial study with economic evaluation. Inclusion criteria are woman (biological), aged ≥ 18 years old and with a report of SUI ≥ once/week. Exclusion criteria are presence of vaginal or urinary infection, virginity, being in the gestational or puerperium period, or neurological disease. Participants will undergo physical therapy assessment and intervention: anamnesis, pelvic floor muscle assessment by vaginal palpation and manometry (Peritron^TM^), questionnaires (Short-Form 6 Dimensions—Brazil (SF-6D), King's Health Questionnaire (KHQ) and King´s Health Questionnaire for Scoring Algorithm), health costs, and voiding diary. Participants will be randomly allocated into 3 groups: CG (control group), IG 1 (intervention group 1, PFMT), and IG2 (intervention group 2, PFMT + NMES). The statistical analysis will be performed by intention to treat, and multivariate analysis of mixed effects will be used to compare outcomes. Effect size measurements will be calculated and will be provided by Cohen’s *d* test. A significance level of 5% will be adopted. Additionally, the incremental cost-effectiveness and incremental cost-utility ratios will be used.

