To assess the presence of urinary symptoms, participants will be instructed to complete a 24-h voiding diary. This instrument contains questions related to the urinary habits, such as the information on number of urinations, amount of urine eliminated, and occurrence of urinary loss. In addition, the voiding diary will quantify the use of absorbents, diapers, and linings (if used and the number of changes) [24, 25]. Participants will be encouraged to complete the voiding urinary twice: once at the pre-treatment before the beginning of the intervention and at the end of the treatment (10th session). The results from the voiding diary will be analyzed by urine loss frequency, considering the urinary leakage associated to stress (e.g., coughing, sneezing, physical exercise or household activities).

Health costs related to UI will be assess by two different questionnaires: (i) SF-6D, validated to Brazilian Portuguese by Campolina et al. [26], and (ii) *King´s Health Questionnaire for Scoring Algorithm*, elaborated by Brazier et al. [27]. The SF-6D evaluates items related to functional capacity, global limitation, physical aspects, emotional aspects, social aspects, pain, mental health, and vitality. This questionnaire allows to generate utility indexes (adjusted by years of life) from data of effectiveness used in economic analyzes. The *King´s Health Questionnaire for Scoring Algorithm* is based on specific health measures of UI, which assesses utility based on quality of life with a five-dimensional classification: functional limitation, physical limitation, social limitation, emotions, and sleep. This questionnaire presents a score of validity pointed in 0.62. Both questionnaires have a unique score ranging from 0 to 1 (where 0 represents the worst health status and 1 represents the better health status) [27].

The psychometric properties of the instruments and procedures are present in Table 2.

**Table 2 Tab2:** Psychometric properties of the instruments and procedures

Examination procedure	Description of procedure	Indicator of musculoskeletal dysfunction	Reported psychometric properties
Modified Oxford Scale (MOS)	Vaginal palpation performed by introduce of two fingers inside participant vaginal canal	Subjective evaluation of PFM function	Intra-rater reliability of MOS (Kappa test) [19] Bidigital palpation 0.75 Inter-rater reliability of MOS (Kappa test) Bidigital palpation 0.60

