### Sample size calculation

The sample calculation was performed to detect an intergroup difference of 5 points at KHQ domains [23] (incontinence impact, daily activities limitations, physical and social limitation, personal relationship, emotions and sleep/energy). An estimated standard deviation of 10 points was adopted, considering three groups, significance level of 5%, power of 85%, and effect size of 0.25. Considering a possible sample loss of 10%, 4 participants will be added per group. Thus, the sample will be composed of 132 women (44 per group).

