**Fig. 3 Fig3:**
[figure not shown]
Scheme of the numbers of sustained, fast contractions, and rest time of the sessions of intravaginal electrical stimulation

The presence of any adverse effects or pain and discomfort related to the application of the NMES will be considered as the criterion to discontinue the treatment. Participants will be instructed to immediately communicate the researcher responsible for the data collection in any case of adverse effect.

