### Statistical analysis plan

The statistical analysis will be performed by a researcher without involvement in the evaluations and treatment intervention. The software SPSS 16.0 and R 3.5.1 will be used for the analysis of data. The level of significance will be set at 5%. The normality of the residues will be verified by the Shapiro-Wilk test.

The comparison of SUI, voiding habits, and quality of life between groups CG, IG 1, and IG 2 and between stages (pre-treatment, re-assessment after finished the intervention protocol and follow-up), as well as the interactions between groups, will be performed by means of analysis of variance (ANOVA) of mixed models considering group and time factors for repeated measures, if the residuals present normality with post hoc contrasts (group IG1 and IG2 versus group CG, and group IG1 versus group IG2).

The first statistical procedure will verify, in general and at each evaluation stage (pre-treatment, re-assessment after finished the intervention protocol and follow-up), if SUI urine loss per day related to stress (e.g., coughing, sneezing, physical exercise or household activities) and quality of life differ into the three groups. The null hypothesis is that all groups will present equal results during outcomes assessments. The alternative hypothesis is that IG 1 will differ from CG and that IG2 will differ from the CG as well.

The second statistical procedure aims to verify if there is alteration in the SUI, urine loss per day related to stress (e.g., coughing, sneezing, physical exercise or household activities), and quality of life throughout the four stages of study evaluation (pre-treatment, re-assessment after finished the intervention protocol and, follow-up of the 3rd and 6th month) within each of the groups. The null hypothesis is that the behavior is the same throughout the stages in each group. The alternative hypothesis is that there is a difference in the stages in each group.

The quantitative variables will be presented as minimum value, maximum value, mean, median, and standard deviation. Categorical variables will be presented as frequencies and percentages.

Details of the statistical analyzes are as follows:

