At the interview and physical assessment, the subjective interview record will be applied, which generates qualitative variables that will be presented as frequencies and percentages and quantitative variables that will be presented as minimum value, maximum value, mean, median, and standard deviation. One researcher will perform the vaginal palpation and the manometry assessment, as well as applied SF6-D, KHQ, King´s Health Questionnaire for Scoring Algorithm, health cost analysis form, and 24 h-voiding diary, which will result in quantitative scales that will be presented as minimum value, maximum value, mean, median, and standard deviation.At the end of treatment sessions, vaginal palpation and manometry will be repeated, as well as SF6-D, KHQ, King’s Health Questionnaire for Scoring Algorithm, health cost analysis form, and the 24 h-voiding diary, which will result in quantitative scales that will be presented as minimum value, maximum value, mean, median, and standard deviation.At the 1st to the 6th month of follow-up, the health cost analysis form will be applied, and at the 3rd and 6th month of follow-up, the SF6-D, KHQ, King´s Health Questionnaire for Scoring Algorithm, and health cost analysis form will be completed, which will result in quantitative scales that will be presented as minimum value, maximum value, mean, median, and standard deviation.At the end of the treatment, the ANOVA for repeated measurements will be applied to verify the effects of the three groups and the two stages (pre-treatment and re-assessment after finished the intervention protocol) and the interactions between them according the results related to the vaginal palpation, manometry, SF6-D, KHQ, King´s Health Questionnaire for Scoring Algorithm, health cost analysis form, and 24 h-voiding diary, if the residues present normality. If the residues do not present normality, a non-parametric test will be applied.At the end of the follow-up, the repeated measures ANOVA will be applied to verify the effects of the three groups and the eight stages (pre-treatment, re-assessment after finished the intervention protocol and 1, 2, 3, 4, 5, and 6 months of the follow-up) and the interactions between them considering the SF6-D, KHQ, King’s Health Questionnaire for Scoring Algorithm, health cost analysis form, and 24 h-VD, if the residues present normality. If the residues do not present normality, a non-parametric test will be applied.The cost-utility assessment will be performed by the quality-adjusted life years (QALY), which combines the length and quality of life into a single index number between 0 and 1, where 0 corresponds to a health state judged to be equivalent to death and 1 corresponds to optimal health [35, 36]. To conduct the statistical analysis, the mean between-group cost differences will be corrected for their baseline, and the total costs will be divided by the costs differences for incremental analysis of cost-effectiveness and cost-utility ratios. Subsequently, a deterministic cost-utility value and a probabilistic one will be determined by applying a bootstrapping technique of 5000 interactions and the bias-corrected, in order to compare health costs between groups. The results will be presented with the confidence interval of 95% (95% CI). The likelihood of the cost-effective intervention will be estimated by the cost-effectiveness acceptability curves to compared values other than willingness to pay [37]. The Kaplan-Meier method and the Log-Rank between-group comparison test will be applied in order to assess the sensitivity of the uncertainty of each parameter by assessing the changes in the results in the range of parameter values [38].

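### The abstract's intention-to-treat, mixed-effects promise is not carried into the itemised rules, whose repeated-measures ANOVA may become a completers analysis

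*Protocol article*

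**What the plan says.** Three places in the protocol article describe the main analysis, and they do not agree.

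- **Abstract, Methods:** "The statistical analysis will be performed by intention to treat, and multivariate analysis of mixed effects will be used to compare outcomes".
- **Statistical analysis plan, general paragraph on SUI, voiding habits and quality of life:** "analysis of variance (ANOVA) of mixed models considering group and time factors for repeated measures".
- **Statistical analysis plan, itemised details:** at the end of treatment "the ANOVA for repeated measurements will be applied to verify the effects of the three groups and the two stages"; at the end of follow-up "the repeated measures ANOVA will be applied to verify the effects of the three groups and the eight stages". If residuals are not normal, a non-parametric test that is not named replaces either one.

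Intention to treat appears in the abstract only.

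Four other statements bear on who would have complete data:

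- The itemised details collect the questionnaires "at the 3rd and 6th month of follow-up, the SF6-D, KHQ", so KHQ and SF-6D exist at four stages: baseline, end of treatment, month 3 and month 6. Evaluation tools has the voiding diary completed only before and at the end of treatment.
- The Interventions section gives one rule for stopping: "any adverse effects or pain and discomfort related to the application of the NMES will be considered as the criterion to discontinue the treatment".
- Measurement of results and Minimizing missing data both tie reassessment to the end of the 10 sessions.
- Sample size calculation: "Considering a possible sample loss of 10%, 4 participants will be added per group".

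**The concern.** Classical repeated-measures ANOVA needs every stage for every woman, and the usual rank tests for paired stages do too. A woman without the end-of-treatment assessment would leave the two-stage analysis even if she later gave KHQ and SF-6D by telephone at months 3 and 6. The analysis would then rest on completers while the abstract, and probably the publication, call it intention to treat.

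Such loss need not be balanced. The only stated criterion for stopping treatment relates to NMES, so it bears on IG2. Reassessment is set by completion of the sessions, and no time is given for a woman who stops early. If some of these women are not reassessed, the IG2 data could be selected on tolerance in the comparison with IG1, which is the contrast that isolates the added NMES.

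Because three descriptions of the model stand side by side, the choice between them could also be made after the data are seen.

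**Working it through.** **1. The three descriptions side by side**

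| Place | Model | Analysis set | Stages |
|---|---|---|---|
| Abstract | mixed effects | intention to treat | not given |
| Analysis plan, general paragraph | ANOVA of mixed models | not given | pre-treatment, reassessment, follow-up |
| Analysis plan, itemised details | repeated-measures ANOVA or an unnamed non-parametric test | not given | two, then eight |

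The middle row can mean a likelihood mixed model, which keeps women with partial data. It can also mean a classical between-within ANOVA, which does not. It therefore does not settle the conflict between the other two rows.

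**2. The plan's own sample size**

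Inputs from Sample size calculation: f = 0.25, three groups, alpha 5%, power 85%. For the between-group factor of a repeated-measures ANOVA, lambda = N x f^2 x m / (1 + (m - 1) x rho). With m = 3 stages and rho = 0.5, both assumed because the article states neither, N = 120 gives lambda = 120 x 0.0625 x 3 / 2 = 11.25 and reaches 85% power.

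- 120 / 3 = 40 per group; 40 + 4 = 44; 44 x 3 = 132, the stated total.
- After the planned loss: 44 x 0.90 = 39.6 per group, or about 40.

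Deleting women at the planned rate therefore leaves the number the trial was sized on. The issue is the analysis set and possible bias, not lost power.

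**3. Share of women kept under listwise deletion**

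If each post-baseline stage is independently missing with probability p (assumed), the complete share is (1 - p)^(stages - 1).

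| p | 2 stages | 4 stages | 8 stages |
|---|---|---|---|
| 5% | 95% | 86% | 70% |
| 10% | 90% | 73% | 48% |

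Combining the planned 10% loss with an assumed 5% sporadic missingness at each of the three post-baseline KHQ stages gives 44 x 0.90 x 0.95^3 = 34 per group (77%).

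Read literally, the eight-stage ANOVA has no complete case at all. KHQ and SF-6D are collected at four of the eight stages and the diary at two.

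**4. Possible bias in IG2 minus IG1**

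This is a large-sample simulation of two stages. Assumptions: SD 10, pre-post correlation 0.5, no true difference, loss in IG2 only. Bias is in KHQ points; negative favours IG2.

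| Loss mechanism in IG2 | Complete case, 10% / 20% loss | Mixed model, 10% / 20% loss |
|---|---|---|
| Random | 0 / 0 | 0 / 0 |
| Worst baseline scores lost | +0.96 / +1.76 | about 0 / about 0 |
| Moderately related to unseen outcome (r = 0.3) | -0.52 / -0.91 | -0.52 / -0.90 |
| Worst post-treatment scores lost | -0.98 / -1.76 | -1.52 / -2.76 |

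Against the 5-point target, 0.96 / 5 = 19% and 1.76 / 5 = 35%. The mixed model removes the bias when loss depends on observed data. It does not when loss depends on the unseen outcome, where it can be worse. The gain from adding months 3 and 6 was not simulated.

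**5. A simple illustration**

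Suppose 10% or 20% of IG2 stop, gain nothing and are unobserved, while the rest gain 5 points. The value over all randomised women is 0.9 x 5 = 4.5 or 0.8 x 5 = 4.0. Completers show 5.0, and 5 / 4.5 = 1.11 and 5 / 4.0 = 1.25, an overstatement of 11-25%. The stopping rates and the zero gain are assumptions.

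**The case against.** The strongest reply is that mixed models are named in the body as well as in the abstract, and the itemised list is introduced as the detail of that paragraph. On this view only terminology is loose. No sentence excludes women with a missing stage, and an article may leave missing-data handling to a plan that is not shown. The last point stands: the lack of a missing-data rule is not itself the finding. But the itemised rules do fix a method, differently from the abstract, and the general paragraph is ambiguous, so the conflict remains.

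Three stronger readings are tempting, and the documents do not support them.

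- **That the plan prescribes a completers analysis.** Deletion follows from how the named method is usually run; it is not a stated rule.
- **That IG2 will be judged only on women who tolerated NMES.** Stopping treatment is not the same as losing the outcome. Nothing says that women who stop are withdrawn or not reassessed, and one who is reassessed stays in her allocated arm under either method. The Discussion also expects few adverse effects.
- **That the cost-effectiveness and cost-utility results lose the same women.** The economic analysis has its own description (baseline-corrected cost differences, bootstrapping), and nothing limits it to complete cases of the ANOVA.

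It is also fair to say that changing the model does not cure every form of loss, as the simulation shows. The diary, a primary outcome, has no later stage from which a mixed model could borrow. Zero gain among women who stop is doubtful too, since all groups are told to exercise daily at home.

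**Conclusion.** The point holds in a limited form. As written, the plan does not secure its own intention-to-treat promise. The abstract, the general paragraph and the itemised rules do not fix one model and one analysis set, and the itemised method, as classically run, drops women with a missing stage and leaves the month 3 and 6 KHQ and SF-6D out of the two-stage analysis.

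The firm part of the size is modest: the planned 10% loss is about 4 of 44 women per group, and the evaluable number stays near 40. Selective loss in IG2 is a risk that the discontinuation criterion and the timing of reassessment make plausible, not an established fact. A reader might infer an 11-25% overstatement in favour of IG2. That figure only illustrates assumed rates, and the direction depends on the mechanism: baseline-dependent loss worked against IG2 in the simulation, and random loss gave no bias. The documents fix neither size nor direction.

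The plan should be amended, because the conflict is plain and cheap to remove before analysis.

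**What to change.** Reconcile the abstract, the general paragraph and the itemised rules to one analysis:

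- **Model:** one likelihood-based mixed-effects model for KHQ and SF-6D with group, time and their interaction. Take both the end-of-treatment and the follow-up contrasts from it, in place of the separate two-stage and eight-stage ANOVAs.
- **Analysis set:** all randomised women in their allocated arm, with every observed value at baseline, end of treatment, month 3 and month 6, whether or not the sessions were completed. Repeat the words intention to treat in the analysis section.
- **Sensitivity analysis:** one analysis that assumes no improvement from baseline for women who discontinued and have missing outcomes. The mixed model alone does not deal with loss related to unseen outcomes.
- **Completers analysis:** label any such analysis as secondary.

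It would also help to state that assessments are sought from women who stop treatment early, and when the end-of-treatment assessment falls for them.

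The cost is wording and slightly more analysis work in R, which the plan already names. No extra participants are needed. The IG2 effect may come out slightly smaller than it would among completers.

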
## Discussion

This study intends to demonstrate whether if SUI and urinary impact in quality of life decrease after a protocol treatment with home exercise guidance without physiotherapeutic supervision and after a protocol of PFMT alone or associated with intravaginal NMES supervised by one physiotherapist. In addition, it is expected that the present study demonstrate the effectiveness, cost-effectiveness, and cost-utility analysis of each proposed treatment. It will be seen in possible changes related to the SUI symptoms of after 10th treatment sessions and during a 6-month follow-up after the end of the treatment.

PFMT is a considered a technique with level of evidence A for the treatment of SUI. However, studies related to the NMES application during SUI are still inconclusive; however, it presents promising results in the treatment of SUI [10]. All the techniques mentioned in the present study are characterized as simple and with minimal occurrence of adverse effects, which facilitates the acceptance of therapy by women who need assistance. As the three groups included in the present study will be instructed to outperform a PFMT protocol daily at home, the addition of the group that will receive guidance only through the booklet will allow us to assess the true effectiveness of the association of PFMT and intravaginal NMES with professional physiotherapist supervision.

In addition, economic analyzes have been decisive in treatment options and may involve direct and indirect costs, with cost measures in monetary value. Then, we will conduct a study that will allow the identification of clinically important outcomes such as the general effectiveness or cost-effectiveness of NMES for SUI treatment in Brazilian women [39], items that are still not described in the previous literature [10].

According to a recently systematic review about scientific evidence of intravaginal NMES in SUI [10], one of the main findings was the low methodological quality of the studies, which may interfere with its reliability and application in clinical practice. Therefore, the present protocol can corroborate with the literature on the effects investigation of the intravaginal NMES associated with PFMT on SUI in addition to the identification of socioeconomic data.

After the conclusion of this research, the results will be presented in journals through peer-reviewed publications and scientific events, including the International Congress.

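### The end-of-follow-up ANOVA covers eight stages, but the KHQ, SF-6D and KHQ scoring algorithm are scheduled at four and the voiding diary at two, so diary urine loss cannot be tested after treatment ends

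*Protocol article*

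**What the plan says.** All references are to the protocol article.

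- **Statistical analysis plan, end-of-follow-up item.** The plan is that "the repeated measures ANOVA will be applied to verify the effects of the three groups and the eight stages". The stages are the pre-treatment assessment and then "re-assessment after finished the intervention protocol and 1, 2, 3, 4, 5, and 6 months of the follow-up". The outcomes begin with "the interactions between them considering the SF6-D, KHQ" and go on to the KHQ scoring algorithm, the cost form and the 24-hour diary.
- **Statistical analysis plan, follow-up collection item.** The cost form is applied monthly from month 1 to month 6. The questionnaires are added only "at the 3rd and 6th month of follow-up, the SF6-D, KHQ" and the KHQ scoring algorithm. The section on primary and secondary outcomes gives the same schedule.
- **Evaluation tools.** On the diary: "Participants will be encouraged to complete the voiding urinary twice: once at the pre-treatment before the beginning of the intervention and at the end" of treatment, which is the 10th session. The diary is the stated instrument for urinary symptoms, a primary outcome.
- **Statistical analysis plan, first and second procedures.** The first compares the groups on stress-related urine loss per day and quality of life at each stage, follow-up included. The second tests change in the same urine loss and in "quality of life throughout the four stages of study evaluation", listed as before treatment, after treatment, month 3 and month 6.
- **Abstract, Methods.** "The statistical analysis will be performed by intention to treat, and multivariate analysis of mixed effects will be used to compare outcomes".
- **Discussion.** "It will be seen in possible changes related to the SUI symptoms of after 10th treatment sessions and during a 6-month follow-up".

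**The concern.** The number of stages is fixed once for a list of instruments that have three different collection schedules. For the questionnaires, half of the stages in the end-of-follow-up model have no planned measurement. For the diary, all six follow-up stages have none.

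The questionnaire mismatch can be put right by rewording, because the four-stage version appears elsewhere in the same section. The diary mismatch goes further. Urinary symptoms are a primary outcome and the diary is how they are measured, yet the plan commits to testing urine loss at follow-up and over four stages. As written, the trial could not say from the diary whether a reduction in leakage lasts beyond the 10th session. An analyst would also have to settle the stages for each outcome after the data are in. A diary not collected at months 3 and 6 cannot be recovered later.

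**Working it through.** **The plan's own figures.** Before treatment + after treatment + months 1 to 6 = 1 + 1 + 6 = 8 stages, which matches the end-of-follow-up item. Before, after, month 3 and month 6 = 4 stages, which matches the second procedure. Each count is correct for its own list. The question is which instruments are scheduled at those stages.

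**Stages by instrument**, from the sections Measurement of results, Evaluation tools and Statistical analysis plan:

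| Instrument | Before | After | Months 3, 6 | Months 1, 2, 4, 5 | Stages |
|---|---|---|---|---|---|
| Cost form | yes | yes | yes | yes | 8 |
| KHQ | yes | yes | yes | no | 4 |
| SF-6D | yes | yes | yes | no | 4 |
| KHQ scoring algorithm | yes | yes | yes | no | 4 |
| 24-hour diary | yes | yes | no | no | 2 |

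**Cells that can be filled.** The model has 3 groups × 8 stages = 24 cells.

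- Cost form: 3 × 8 = 24 filled, 0 empty.
- KHQ, SF-6D and KHQ scoring algorithm: 3 × 4 = 12 filled, 12 empty.
- Diary: 3 × 2 = 6 filled, 18 empty.

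The rank of the 24-cell design restricted to the scheduled stages equals these counts: 24, 12 and 6.

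**Interaction degrees of freedom**, (groups − 1) × (stages − 1):

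- Eight stages, as written: 2 × 7 = 14.
- Four stages, as the questionnaires support: 2 × 3 = 6.
- Two stages, as the diary supports: 2 × 1 = 2.

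The written group-by-stage test is therefore not the one the questionnaire or diary data can supply. A mixed model keeps every woman with at least one record, but it still cannot estimate an effect in a cell where nobody is measured.

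**The four-stage tests.** Quality of life has four planned stages and four scheduled collections, so it matches. Urine loss per day has four planned stages and two scheduled collections, so months 3 and 6 are empty.

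**What can be run as written.** The end-of-treatment item uses two stages, and every instrument it lists is collected at both.

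**The case against.** The strongest defence is that the eight stages are simply the union of the collection times across the listed instruments. They are right for the cost form, and any analyst would use for each outcome the stages at which it was measured. Much of this stands for the questionnaires, because the second procedure already gives their correct four stages. It does not help the diary. The end-of-follow-up list leaves out palpation and manometry, which are not collected in follow-up, but keeps the diary. A reader cannot tell whether that is a slip or an intention to collect it.

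The outcomes section does say in general terms that outcomes are evaluated by telephone for 6 months. Its next sentence limits the questionnaires to the 3rd and 6th assessments, and Evaluation tools limits the diary to two completions. The schedule figure is not available here. If it showed follow-up diaries, it would contradict that limit and would itself need reconciling. The non-parametric fallback does not help either, since it would face the same empty stages.

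Some stronger readings are tempting, but the documents do not support them:

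- **The primary outcomes cannot be analysed at all.** The before/after analysis covers them all, and the four-stage quality-of-life analysis fits the schedule.
- **All 132 women are lost as incomplete cases.** No woman can have eight KHQ or diary values, but that restates the mismatch and is not a loss of data. Nothing in the article prescribes listwise deletion, and both the Abstract and the general paragraph of the Statistical analysis plan name mixed models. A conflict with intention to treat is therefore an inference from a label.
- **No symptom information exists in follow-up.** The KHQ is given at months 3 and 6 and includes severity measures. What is missing is the diary's urine loss per day.

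**Conclusion.** The point holds as an internal contradiction between the analysis and the collection schedule. The eight-stage model is estimable for the cost form only. Effects at months 1, 2, 4 and 5 cannot be estimated for the three questionnaire measures (12 of 24 cells empty), nor at any follow-up month for the diary (18 of 24 empty). This is so under any model and even with perfect retention. The tests of stress-related urine loss at follow-up and over four stages have no data beyond the end of treatment.

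The consequence is limited to those items. The before/after analysis and the four-stage quality-of-life analysis stand. The Discussion's statement about symptoms during follow-up lacks diary support but has some support from the KHQ.

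The conclusion rests on the article's text alone and assumes that the written schedule is the one carried out. It needs no assumption about dropout. A calculation of how many women would have complete monthly records would need completion rates that the article does not give, and it would concern only the cost form, where eight stages is correct.

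**What to change.** 1. **State the stages for each instrument** in the Statistical analysis plan: KHQ, SF-6D and KHQ scoring algorithm at four (before, after, months 3 and 6); cost form at eight; diary, palpation and manometry at two.
2. **Settle the diary.** There are two options.
   - Collect the same self-completed 24-hour diary at months 3 and 6, which makes it a four-stage outcome. This costs two more one-day diaries per woman and is possible only while those contacts are still to come.
   - Keep the diary at two stages. Remove diary urine loss from the follow-up comparison, the four-stage test and the end-of-follow-up item, and limit the Discussion's follow-up statement to what the KHQ measures. This costs wording only, and gives up any diary-based conclusion about durability.
3. **Use one name for the model.** In the detailed items, replace repeated-measures ANOVA with the mixed-effects approach already named in the Abstract and in the general paragraph, and say that all observed records of randomised women are used. Choose the form to suit each outcome: a linear model for everything would fit poorly with a 0–5 palpation grade and 24-hour leakage counts. R, already named in the plan, can fit such models.
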